## Abstract

**Background:**

Gait automaticity, the ability of the brain to control locomotion with minimal use of executive-attentional resources, is altered in people with Parkinson’s disease (PD). Recently, we showed that step-synchronized tactile cueing improved gait regularity and freezing of gait in PD; however, it is not known if this cueing mode also improves gait automaticity. Thus, this study investigates the effects of step-synchronized tactile cueing (versus fixed cueing) on gait automaticity in the laboratory and during daily life.

**Methods:**

This is a pilot, randomized, double-blinded study where sixty participants with PD will be randomized into one of two, cueing interventions: 1) personalized, step-synchronized tactile cueing and 2) tactile cueing at fixed intervals. Both cueing interventions use vibrotactile stimulation of wrist bands. During a laboratory study visit, we will measure cortical activity with a wireless, portable functional near-infrared spectroscopy system (fNIRS) during walking tasks. Gait will be assessed using inertial sensors placed on the limbs and trunk. In addition, in daily life, participants will use the same cueing mode at home. The primary outcomes include prefrontal & primary sensory cortex activity. Secondary outcomes are gait stride time, gait local dynamic stability, turn duration and trunk jerk during turning as metrics of gait automaticity in the laboratory. Daily life gait and turning are exploratory measures.

**Discussion:**

This project will advance the understanding of brain mechanisms associated with walking automaticity during tactile cueing and provide the basis for innovative, personalized cueing to rehabilitate gait automaticity in people with PD.

**Trial registration:**

ClinicalTrials.gov NCT05818189.

## 1. Background

Gait automaticity, defined as walking with minimal cognitive effort [1], is a hallmark of healthy gait and it is typically governed by a distributed network, including the spinal cord, brainstem, cerebellum, basal ganglia and sensorimotor cortical areas [2–4]. In normal conditions, cognitive control regions (i.e., prefrontal cortex) remain minimally active unless the task or environment is novel or highly challenging [5].

In Parkinson’s disease (PD), gait abnormalities are often linked to a shift from brain automaticity to compensatory executive control [6]. This shift places increased demands on limited cognitive resources, and may negatively impact functional walking performance [7]. Impaired basal ganglia function likely contributes to this loss of automaticity [1].

To better understand gait automaticity, both neural and behavioral correlates must be studied [8–10]. While direct access to subcortical activity during gait is limited, cortical activity can be captured using EEG or functional near-infrared spectroscopy (fNIRS) [11,12]. Behaviorally, gait and turning quality can be measured objectively [13] and further evaluated under dual-task conditions to increase cognitive load [14].

EEG studies report increased activity in the prefrontal cortex (PFC), supplementary motor area (SMA), motor cortex, and sensorimotor cortex while walking in people with PD compared to healthy controls [15,16]. Such an overall increase in cortical activity while walking is consistent with functional magnetic resonance imaging (fMRI) studies while participants were lying in the scanner and operating a foot pedal mimicking walking [8]. fNIRS studies also report elevated PFC activity in PD during single-task walking, though findings during dual-task conditions are mixed [17,18]. Methodological inconsistencies, such as variability in signal processing, have limited generalizability across studies [11,19]. While the PFC is the most studied region, a few fNIRS studies have also explored other cortical areas during walking in people with PD [11,20].

Behaviorally, increased variability in gait (stride time, stride length, gait speed variability) [8,21] and impaired turning (velocity, smoothness) [22,23] have been associated with reduced automaticity. In healthy older adults, such variability remains stable during dual-task walking, whereas in PD, variability increases, suggesting increased reliance on cognitive control [24,25]. Turning appears particularly sensitive to automaticity loss [22]. However, gait and turning variability can also be influenced by freezing of gait (FOG) and postural instability, complicating interpretation [21,26]. Therefore, increased variability during gait and turning may not necessarily represent an automaticity decrement, so measuring cortical activity directly while walking would help validate automaticity changes [10]. Additionally, other studies show that very low and very high gait variability (U-shaped trend) could be associated with subclinical basal ganglia damage [27]. Thus, combining cortical and behavioral measures together may offer a more complete understanding of gait automaticity in PD, critical to developing improved rehabilitation strategies.

Current treatments for PD, such as levodopa or deep brain stimulation, do not reliably improve automaticity in PD. Levodopa does not improve, and may worsen, balance and attention [28,29], while deep brain stimulation offers limited benefits for balance or cognitive function [30]. As a result, alternative and complimentary interventions are needed.

Cueing, using external temporal or spatial stimuli like auditory, visual, or tactile stimuli [31], can improve gait, turning, and FOG [32]. Its effects vary depending on the cueing modality, medication state, and individual impairments [32]. However, the neural mechanisms underlying cueing remain unclear, particularly its impact on cortical areas like the PFC [33–36]. If cueing with external stimuli while walking requires increased cortical attention, we will see increased PFC activity, whereas if cueing improves automaticity, we will see decreased PFC activity. Thus, it is necessary to better understand the impact of different cueing modalities on the cortical and behavioral correlates of automaticity, to improve the effectiveness of cueing [37].

This study aims to evaluate personalized tactile cueing, synchronized to an individuals’ gait rhythm [38], on gait automaticity. The current use of cueing in rehabilitation predominantly uses cues in a fixed, open-loop manner (i.e., constant rhythmical sounds or vibrations, or visual cues as tape on the floor) rather than a personalized, closed-loop manner of cueing (i.e., intermittent stimuli set to the individual’s personal walking pace) [38]. This personalized mode of cueing has demonstrated a higher degree of gait and posture improvement and longer lasting effects compared with open-loop cueing [38–40]. Tactile cues may also engage more subcortical (automatic) pathways than visual or auditory cues [38], supporting proprioception and somatosensory integration, functions often impaired in PD [41–44].

Our previous work [38,40] showed that personalized, tactile cueing reduces FOG during turning in people with PD and improved gait stability, measured by local dynamic stability, during walking in people with PD. These effects may stem from enhanced proprioceptive feedback via cerebellar pathways. Early findings also suggest improvements in gait asymmetry and rhythmicity with peripheral tactile stimulation [45].

This study aims to test the feasibility and impact of using tactile cueing on gait in daily life. Since motor learning and gait automaticity depend on repetition [46], practicing cueing during everyday mobility may lead to longer-term improvements than cueing limited to clinic or laboratory sessions. Although several studies have trialed home-based cueing [31,47,48], they lacked objective gait and turning metrics in daily living, limiting insights into effects of cueing on gait regularity.

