### 3.4. Assessment procedures

#### 3.4.1. General procedures.

Fig 2 below illustrates the flow of study activities. After screening and randomization, the immediate effect of the cueing interventions will be assessed during a study visit to the laboratory (Visit 1) through measures of cortical activity and functional mobility. Additionally, clinical and cognitive scales will also be conducted during this visit.

The main outcomes will be measured in the ON-medication state (after approximately 1-hour from last intake) before and while using their assigned tactile cueing mode (personalized or fixed). During the assessment, participants will complete the following mobility tasks, first without cueing and then with cueing activated: 1) 2-minute walking, 2) 2-minute walking with a concurrent cognitive dual-task, 3) 1-minute 360 degrees turning in place, and 4) 1-minute 360 degrees turning in place with a concurrent cognitive dual-task.

The gait task consists of two minutes of walking back and forth along a 9-meter hallway at comfortable speed. The turning task involves alternating 360° turns (right and left) in place for one minute. The secondary cognitive task used in both dual-task conditions is a modified version of the Continuous Performance Test–AX (AX-CPT), which assesses attention and vigilance.

Throughout the mobility protocol, participants will wear a portable fNIRS system (Brite and OctaMon, Artinis) and three wireless inertial sensors (APDM Precision Motion, Clario) positioned on the posterior trunk and both feet to objectively measure cortical activity while performing gait and turning tasks.

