**Primary outcome in bold.**

In the laboratory, during walking trials, stride time variability (a key marker of automaticity) will be calculated as the coefficient of variation of stride time. Phase-dependent local dynamic stability (LDS) will be estimated using methods previously described in [40]. For the 360° turning in place task, we will analyze the yaw angular velocity from the posterior trunk sensor to compute [70] the average turning duration, number of steps in turn, and the average jerkiness of the turns.

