#### 3.5.2. Statistical analysis.

The primary outcome will compare PFC and sensory cortex HbO2 while walking and turning between personalized tactile cueing and fixed tactile cueing groups measured during Laboratory Visit 1, without and with cueing. We will average the HbO2 concentrations over 2-minutes of walking (and over 1-minute of 360-degree clockwise and counterclockwise turning), then compare within-subject effects (baseline versus cueing) and between-subject effects (personalized versus fixed cueing) in a repeated measures analysis. Specifically, we will apply mixed-effects models with HbO2 levels (averaged over walking bout) for each person at each assessment time point as the dependent variable. We will include as independent variables: (i) indicator variable for group assignment (personalized or fixed cueing), (ii) indicators for time points (baseline, cueing), and (iii) group by assessment interaction terms. Randomization stratification variables, Hoehn and Yahr, FOG and cognitive status, will be entered into the model as covariates. A random subject intercept will account for correlation between the two repeated measurements within each subject.

Similar linear mixed effects models will be used to demonstrate improvement in walking and turning metrics in the laboratory (carried out with the fNIRS measurements), secondary outcomes. Significance level will be set at 0.05 for testing whether coefficients are different from 0 for primary and secondary outcomes.

We will employ similar linear mixed effects models to investigate whether the two cueing modalities will result in different improvements of walking and turning during daily life. This is an exploratory analysis. For the week of daily mobility without and with cueing, we will summarize walking and turning measures at home (outlined on Table 1) by computing the average over 7 days of daily activity, considering only the recordings with more than 7 hours per day and at least 5 days (Table 1). Randomization stratification variables, Hoehn and Yahr, freezing of gait and cognitive status, will be entered into the model as covariates. Additional covariates would be the life space assessment and activity levels. The effect sizes from models fit for this pilot study will be used to determine the number of subjects required for a future clinical trial.

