Another aspect of innovation is the fact that our cueing system is standalone, app-free design, allowing users to benefit from tactile cueing without relying on smartphones or external devices. The tactile stimulus occurs on simple bracelets on the wrists, which are easy to don and provides perceptible vibration to people with PD, who usually cannot detect vibration on the feet [76]. The cueing system has a simple switch to turn the stimulation on or off. This simplicity is especially important for people with Parkinson’s disease, who may experience cognitive or motor challenges that make app navigation difficult. By eliminating the need for digital interfaces, the system may enhance usability, accessibility, and real-world adherence, making it a practical solution for unsupervised use in daily life. The device’s personalized, closed-loop algorithm still operates in real time based on the user’s gait, delivering tailored cues, while maintaining a user-friendly, low-tech interface, which is a novel feature in the field of gait rehabilitation.

Furthermore, using instrumented socks allows for unobtrusive and continuous monitoring of gait in daily life, providing a rich dataset to evaluate how cueing affects mobility outside the laboratory. Likewise, the sensor on the elastic belt around the waist provides accurate measures of turning quality in daily life. By bridging neural, behavioral, and ecological data, this study can help next-generation, personalized rehabilitation strategies in PD and as well as other groups with gait impairments. Gait automaticity, or the ability to multitask while walking, is a critical, functional skill that may be improved with the addition of appropriate rehabilitation, such as cueing.

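### The stated laboratory model has no task term: it cannot separate steadier gait in both tasks from a smaller dual-task rise in variability, and it omits the task-by-group interaction that was powered

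*Protocol article*

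**What the plan says.** **Behavioural signs of automaticity.** Section 1 (Background) gives two. The first is the level of variability: it associates "increased variability in gait (stride time, stride length, gait speed variability" and impaired turning with reduced automaticity. The second is the response to a dual task: "In healthy older adults, such variability remains stable during dual-task walking, whereas in PD, variability increases, suggesting increased reliance on cognitive control". Section 4 (Discussion) describes the construct as "Gait automaticity, or the ability to multitask while walking".

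**Outcomes.** Section 3.4.4 (Gait and turning assessment) says that "stride time variability (a key marker of automaticity) will be calculated as the coefficient of variation of stride time". The Abstract presents the secondary laboratory outcomes as measures of gait automaticity. Table 1 also lists mean stride measures, local dynamic stability and turning measures.

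**Data collected.** Section 3.4.1 (General procedures) schedules plain walking, "2-minute walking with a concurrent cognitive dual-task", and the same pair of tasks for turning. All are done first without and then with cueing, so each activity has four cells per participant.

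**Model.** Section 3.5.2 (Statistical analysis) lists group, "indicators for time points (baseline, cueing", and the group-by-assessment interaction, plus covariates. It adds: "A random subject intercept will account for correlation between the two repeated measurements within each subject". Laboratory gait and turning get models of the same kind. No task term appears.

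**Power.** Section 3.5.1 (Power analysis) gives 82% for the between-group test and 94% for an interaction of cueing group with dual- versus single-task walking, both for HbO2.

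**The concern.** The design collects what is needed to ask whether cueing protects gait when attention is loaded, but the stated model does not ask it. A cue that makes steps more regular to the same degree in both tasks, for example by pacing, lowers stride-time CoV without changing how much CoV rises under the dual task. A cue that acts mainly under cognitive load shrinks that rise. Both are of interest, but they mean different things for automaticity, and the stated terms do not distinguish them.

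Because the secondary outcomes carry an automaticity label, a reader of the results could take a lower CoV as evidence of improved automaticity in either case. In addition, the interaction that supports the stated 94% power has no counterpart in the analysis section, even for the primary HbO2 outcome.

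**Working it through.** **1. The plan's own figures.** Recruitment of 60 less 10% gives 60 × 0.9 = 54, or 27 per group, as stated. The 82% and 94% cannot be reproduced forward, because no HbO2 means or differences are given. They can be back-solved.

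Inputs from section 3.5.1: n = 27 per group, variance s² = 0.08, correlation ρ = 0.2, alpha 0.05 (taken as two-sided). With two within-subject levels the F-test is a t-test with 2n − 2 = 52 degrees of freedom and noncentrality δ/√(2v/n), where v is the per-participant variance of the contrast.

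- Between-group test: v = s²(1 + ρ)/2 = 0.08 × 1.2/2 = 0.048. Power of 82% needs δ = 0.175 (0.62 SD).
- Group-by-task interaction: v = 2s²(1 − ρ) = 2 × 0.08 × 0.8 = 0.128. Power of 94% needs δ = 0.349 (1.23 SD).

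If 0.08 is only the between-subject component, the total variance is 0.08/0.2 = 0.4. The differences become 0.391 and 0.780, the same in SD units.

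**2. Terms against cells.** For walking, 2 tasks × 2 cueing states = 4 rows per participant are measured. The model has 2. Either the tasks are averaged or each task is modelled separately; the article does not say which.

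**3. Can the stated terms tell two effects apart?** Assumed CoVs without cueing: single task 3.0%, dual task 4.0%; no change in the fixed arm.

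| Personalized arm with cueing | Single | Dual | Group × time, averaged over tasks | Dual-task cost before → after | Group × cueing × task |
|---|---|---|---|---|---|
| (a) 0.5-point drop in both tasks | 2.5 | 3.5 | (−0.5 − 0.5)/2 = −0.5 | 1.0 → 1.0 | 0 |
| (b) 1.0-point drop in dual task only | 3.0 | 3.0 | (0 − 1.0)/2 = −0.5 | 1.0 → 0 | −1.0 |

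Averaged over tasks, (a) and (b) are identical. Separate models per task would show the different drops but would give neither an estimate nor a test of the change in cost.

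**4. The scale matters.** In (a) the absolute cost is unchanged, but the relative cost goes from 1.0/3.0 = 33% to 1.0/2.5 = 40%. On the log scale it goes from ln(4.0/3.0) = 0.288 to ln(3.5/2.5) = 0.336.

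**5. Price in precision.** Take variance s² in each cell and a common correlation r.

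- Change with cueing in one task: variance 2s²(1 − r).
- Change in dual-task cost: variance 4s²(1 − r).
- Ratio 2, so the standard error is √2 = 1.41 times as large.

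On the HbO2 inputs, v = 4 × 0.08 × 0.8 = 0.256. The difference of 0.349 that gave 94% power then gives about 70% at 27 per group, and about 53 per group would be needed for 94%. This takes 0.08 as the variance of HbO2 in a single condition. If it were the variance of a cueing-minus-baseline change, the powered interaction would already be the three-way contrast; the article does not say. It gives no inputs for laboratory CoV.

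**The case against.** The strongest objection is that analysing CoV with and without cueing follows the protocol's stated marker. The Background names the level of variability first, and section 3.4.4 makes stride-time CoV the marker. A reader might infer that the dual-task rise is the protocol's only behavioural sign, and that an equal drop in both tasks would be declared improved automaticity. The documents support neither step:

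- Section 2 (Objectives) attaches improved automaticity to lower prefrontal activity. The Discussion bases support for the hypothesis on a prefrontal decrease and a sensory increase with personalized cueing only.
- The Discussion expects lower stride-time variability with both cueing modes, so on that account CoV does not decide the question.
- The Background's caution is that "increased variability during gait and turning may not necessarily represent an automaticity decrement, so measuring cortical activity directly while walking would help validate automaticity changes". It is prompted by freezing and postural instability, and its remedy is cortical measurement, not dual-task cost.
- A dual-task CoV that falls from 4.0% to 3.5% can fairly be called better walking while multitasking.
- Table 1 is not limited to CoV.

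All of this stands, and it rules out replacing the stated secondary outcome with dual-task cost.

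It can also be said that task handling belongs in an analysis plan that is not shown, and that two measurements per participant fits separate models per task. This stands only in part. The article does not leave the model open: it lists the terms and the number of repeated measurements. Separate models still do not estimate the change in cost, and the powered interaction is missing from the listed terms.

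**Conclusion.** The point holds as a gap in the stated analysis, not as a wrong choice of marker. The laboratory model cannot separate an equal fall in variability across tasks from a smaller dual-task rise, although the protocol treats performance under a dual task as part of automaticity and measures every cell needed. It also lacks the task-by-group interaction powered for HbO2, so sections 3.5.1 and 3.5.2 do not match.

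The consequence is confined to interpreting the secondary gait and turning outcomes and to that mismatch; the main automaticity conclusion rests on prefrontal and sensory cortex activity. The CoV values are illustrative assumptions, and the factor of 1.41 assumes equal variances and correlations across conditions. The fall from 94% to about 70% further assumes the stated HbO2 inputs and an effect of the same absolute size.

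**What to change.** In section 3.5.2:

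1. For each laboratory measure, fit the mixed model to all four task-by-cueing rows per participant, with group, cueing, task and their interactions. Do the same for HbO2, so that the analysis contains the interaction on which section 3.5.1 bases its power.
2. Keep the change in CoV with cueing as the stated secondary outcome.
3. Add the arm difference in change of dual-task cost of stride-time CoV (group × cueing × task) as a supportive estimate with its confidence interval, and fix its scale, absolute or log, in advance.
4. State that a fall in absolute CoV will be interpreted alongside that contrast and the cortical results.

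No new measurement is needed; only the analysis text changes. The cost is precision: the standard error is about 1.41 times that of a single-task change, so with 27 per group the contrast should be reported as an estimate and not as a powered test.

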## 2. Objectives

The primary objective of this trial is to assess immediate changes in cortical activity during walking with two types of tactile cueing in people with PD, and whether these changes are accompanied by improvement in gait and turning (laboratory testing). We hypothesize that personalized tactile cueing will reduce PFC activity (improve automaticity) and reduce gait variability (as well as improve gait and turning speed). We also expect to observe increased activity in the primary sensory cortex with this type of personalized cueing that may require sensorimotor planning. In contrast, we predict that the fixed cueing will increase PFC activity and increase gait variability (need for more attention to the cues). An exploratory objective is to evaluate the feasibility and potential benefits of using tactile cueing during daily life.

